#### Effects

In health economics the effects of interventions under evaluation are preferably expressed in QALYs.^15^ Research on QALYs of different dialysis modalities is widespread,^8 20 21^ but instruments and patient background variables vary. Therefore, we are currently in the process of collecting quality of life data from both patients who are yet to start RRT and dialysis patients prior to the intervention, through the 5-level version of EuroQol-5 Dimension (EQ-5D-5L), the quality of life instrument recommended in the Dutch guidelines for health economics.^16^ We also collect quality of life data from patients after the intervention. The educators administer the EQ-5D-5L questionnaire to patients at baseline, 6, 12 and 24 months after the intervention by telephone.

#### Markov model

To assess the cost-effectiveness of the implementation of the home-based educational programme, we will build a ‘Markov simulation model’. This model will assess the costs and effects of ESRD treatments as it simulates the course of treatment and disease of the patients. The model will have a similar structure as a previously published model on this population,^7^ with some important updates and improvements. Unlike that Markov model, which used multivariate and univariate sensitivity analyses,^7^ our model will include probabilistic sensitivity analysis using Monte Carlo simulation. Consequently, uncertainty of all values is considered simultaneously, and the uncertainty in each parameter is assumed to possess a probability distribution.^22^ The model will run 10 000 simulations in Microsoft Excel, V.2010. By using probabilistic sensitivity analyses we follow current guidelines in health economics.^16 23 24^ A Markov modelling technique is applicable because the decision problem involves risk that is continuous over time, the timing of events is important and events may happen more than once.^25^ Within a Markov simulation, the time horizon of the study is divided into a number of discrete time periods, the so-called Markov cycles. A Markov process is based on the idea that patients are always in a certain disease state and that they can change between disease states once during each cycle. By assigning effects to each disease state and keeping track of the time patients remained in each disease state, long-term effects can be calculated. For this cost-effectiveness analysis the effects and cost per health state do not change because of the intervention. We expect that there will be more LDKTs because of the intervention. Therefore, besides the costs of the programme, only the transition probabilities will change because of the intervention and will be the only difference between the baseline and the post implementation situation. Table 1 shows an overview of the parameters used and the source.

**Table 1 T1:** Overview of parameters and sources in the Markov model

Parameter	Sources
Costs Medical costs Intervention costs Costs of productivity losses Informal care costs	Cost study of RRT in the Netherlands by [name] *et al* (forthcoming) Are recorded in the current implementation study Work situation of patients is recorded in the implementation study and use of (Dutch) literature.^16 17^ Will be estimated from existing literature^18^
Effects (QALYs)	EQ-5D-5L is conducted prior to the intervention and 6, 12 and 24 months after the intervention.
Transition probabilities Between treatment modalities Mortality rate	Estimated from the database of Nefrovisie
Incidence rates	Estimated from the database of Nefrovisie
Effect size of the intervention	Used from previous studies^3 4^

EQ-5D-5L, 5-level version of EuroQol-5 Dimension; QALY, quality-adjusted life years; RRT, renal replacement therapy.

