### Hypotheses

Previous research has provided convincing evidence that transplantation costs less, gives a better survival and a higher quality of life compared with dialysis.^7–9^ We therefore hypothesise that the relatively small incremental costs of the home-based educational programme should be cost-effective. Since it is desirable that in the future all waiting list patients can benefit from the effects of the home-based intervention, this programme should be part of standard care. Hence, a solid basis of the cost-effectiveness of that educational programme is warranted.

The second hypothesis is that higher protocol adherence among healthcare providers will be associated with more positive effects of the educational interventions. These effects include an increase in knowledge of renal disease and the treatment options, an increase in communication with family/friends about RRTs, an increase in living kidney donation activities and an increase in QALYs. If a relationship between protocol adherence and effects is shown, a quality assurance system should be an inseparable part of the educational programme.

The third hypothesis is that a full implementation of the educational programme leads to policy implications regarding care for patients with ESRD. Full implementation may affect the need for dialysis centres and transplantation facilities. By modelling the prevalence we can estimate the need for allocating the healthcare budget. We aim to present the outcomes of the model in a budget impact analysis (BIA).

Thus, the main aim of this article is to discuss the protocol of the cost-effectiveness study of the home-based educational programme and of the quality assurance programme which are currently being implemented in the Netherlands. Additionally, potential policy implications of our hypotheses are discussed in this article.

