### Cost-effectiveness

#### Costs

The latest published research on costs of dialysis and transplantation in the Netherlands dates back from the late 1990s.^7^ Currently, research on costs of dialysis and transplantation is in its final phase. We will use this forthcoming data ([name], personal communication). This cost data is of high quality, as it is based on the national database of insurance companies from 2014, which consists of records from 99% of all Dutch citizens. Cost calculations will include costs of dialysis modality, dialysis access, transplant procedure, other hospital costs, primary care costs, mental healthcare, medication outside the hospital, medical devices, healthcare abroad, transport and other costs. Healthcare costs for transplantation include preparatory research, transplant operation, guidance, after care, donor expenses, dialysis procedure, other hospital costs, primary care, mental healthcare, medication outside hospital, medical devices, healthcare abroad, transportation and other costs. These include all the healthcare costs associated with RRT. Since it is recommended that cost-effectiveness analysis is conducted from a societal perspective, we also aim to calculate the productivity costs.^15^ Productivity costs will be estimated with the friction cost method, as recommended in the Dutch guidelines for economic evaluation.^16^ Besides that the work situation of patients participating in the study is recorded, some research has been done regarding labour participation of patients with ESRD.^17 18^ The costs of the home-based intervention and the quality assurance will be estimated on the basis of the current practice in the implementation. Informal care costs will be estimated from the literature.^19^ The costs of the intervention are recorded per centre.

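### The costing rule gives extra living-donor work-ups that end without a transplant no route into incremental cost, except in proportion to completed transplants

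*Protocol article*

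**What the plan says.** The rule is in the Markov model section. It first fixes state values: "For this cost-effectiveness analysis the effects and cost per health state do not change because of the intervention". It then says that, programme costs aside, "only the transition probabilities will change because of the intervention and will be the only difference between the baseline and the post implementation situation".

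The Costs section describes what programme costs cover: "The costs of the home-based intervention and the quality assurance will be estimated on the basis of the current practice in the implementation". Donor evaluation is not named there. It appears on the transplant side: "Healthcare costs for transplantation include preparatory research, transplant operation, guidance, after care, donor expenses, dialysis procedure, other hospital costs". The more general list is broad: "Cost calculations will include costs of dialysis modality, dialysis access, transplant procedure, other hospital costs, primary care costs". The section adds that these items cover all healthcare costs linked to renal replacement therapy (RRT). The medical costs come from a forthcoming study, of which the article says that "it is based on the national database of insurance companies from 2014, which consists of records from 99% of all Dutch citizens".

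The Markov states section lists dialysis modalities and transplantation, each split into first and later years. It lists no work-up state and no state before RRT.

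Under Hypotheses, the expected effects of better protocol adherence include "an increase in living kidney donation activities and an increase in QALYs". The abstract says that data on LDKT activities will be taken from medical records up to 24 months after the education. Table 1 does not list them as a model input.

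**The concern.** Participants and procedure restricts the offer to patients who have not found a donor candidate in their network. The second session brings family and friends into the discussion. If this works, more people will present for evaluation, and some will not donate. Under the stated rule, such a work-up is not a listed programme cost, triggers no transition, and cannot raise the cost of the dialysis state in which the patient remains. A patient who has not yet started RRT has no listed state to which the cost could attach.

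At stake are incremental cost, the cost-effectiveness ratio and the budget impact analysis, which are meant to support reimbursement. The planned probabilistic analysis does not repair this, because it varies state costs that are common to both scenarios. The sensitivity analysis described under Outcomes concerns the size of the effect on LDKT.

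**Working it through.** **1. The plan's own figure.** The Introduction gives 17 vs 4 LDKTs among 163 patients, p=0.003. The ratio is 17/4 = 4.25, which agrees with the claim of four times more. Arm sizes are not given. With arms of 81 and 82, Fisher's exact test gives p = 0.0022 and Pearson's chi-square 0.0021; with 82 and 81 they give 0.0041 and 0.0026. The reported p-value is consistent with near-equal arms, so I assume 81.5 per arm.

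- Risk difference: (17 − 4)/81.5 = 0.1595.
- Educations per extra LDKT: 81.5/13 = 6.27.
- Volume, from Participants and procedure: 4 × 50 + 4 × 20 = 280 a year, or 560 over 2 years, giving 560 × 0.1595 = 89 extra LDKTs. If the regional figure of 20 is a total and not a yearly number, the volume is 4 × 50 × 2 + 4 × 20 = 480, giving 77.

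**2. What the rule charges.** Let *f* be the extra failed donor work-ups per extra LDKT caused by the programme, *r* the failed work-ups per LDKT already averaged into the transplant unit cost, and *w* the cost of one work-up. The cost missed per extra LDKT is *w* × (*f* − *r*).

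- Unit cost excludes failed work-ups: *r* = 0, and all of *f* is missed.
- Unit cost includes them and they rise in step with LDKTs: *f* = *r*, and nothing is missed.
- Unit cost includes them and they rise faster: only the excess *f* − *r* is missed.
- Unit cost includes them and they rise more slowly: *f* < *r*, and the bias runs against the programme.

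The article gives none of *f*, *r* or *w*.

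**3. Illustration over assumed ranges.** The excess *f* − *r* and the cost *w* are both assumptions. Cells show EUR missed per extra LDKT, with EUR per educated patient (× 0.1595) in brackets.

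| Excess per extra LDKT | w = 1,000 | w = 3,000 | w = 5,000 |
|---|---|---|---|
| 0 | 0 (0) | 0 (0) | 0 (0) |
| 0.5 | 500 (80) | 1,500 (239) | 2,500 (399) |
| 1 | 1,000 (160) | 3,000 (479) | 5,000 (798) |
| 2 | 2,000 (319) | 6,000 (957) | 10,000 (1,595) |

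Over 560 educated patients, an excess of 0.5, 1 or 2 corresponds to about 45, 89 or 179 uncounted work-ups.

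**4. Scale.** At an assumed EUR 1,000 to 2,000 per education, programme cost per extra LDKT is 6.27 times that, about EUR 6,269 to 12,538. The upper part of the table is of that order and the lower part is far below it. Programme cost is only one component of incremental cost: each extra LDKT also brings transplant-state costs and removes dialysis costs, for which the article gives no figures.

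**The case against.** The strongest reply is that the unit costs may already contain failed work-ups. They are averages from near-complete national insurer records, the transplant list includes preparatory examinations and donor expenses, and both cost lists have a broad category for other hospital costs. What the averages contain is settled in a cost study not shown here, and an article may leave that detail elsewhere. This stands, and it rules out several stronger readings.

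- A reader might infer that failed work-ups are costed at zero. The article does not say so, and baseline-level failures may already be included.
- A reader might infer that the missing cost arises only with the programme. Work-ups also occur without it: the trial's control arm had 4 LDKTs, and the Implementation section says that standard care in Rotterdam already promoted living donation. Only an excess matters.
- A reader might treat LDKT activities as clearly distinct from completed transplants. The term is undefined. The Introduction names it as the third outcome, where the Discussion's section on quality assurance names the number of transplantations.
- A reader might extend the point to recipient work-up. That is weaker, because enrolled patients must already be eligible for transplantation.

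The reply does not remove the point. Even if failures are averaged in, the rule charges them only per completed LDKT, at the ratio in the 2014 data. Nothing in the article suggests that patients who had found no candidate would share that ratio. This is a rule that the article states, not a detail it leaves out.

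**Conclusion.** The concern holds in a limited form. The rule leaves extra failed donor work-ups no route into incremental cost beyond what the transplant unit cost may carry in proportion to completed LDKTs. If the programme raises failed work-ups by more than that proportion, the bias favours the programme.

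The direction is conditional on that excess, and the document does not determine the size. The illustrative EUR 80 to 1,595 per educated patient (EUR 500 to 10,000 per extra LDKT) rests on assumed work-up costs, an assumed excess and near-equal trial arms; with no excess it is zero.

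A reader might go further and infer that the programme would cease to be cost-effective. The document does not support that. It describes dialysis as costly and transplantation as cheaper, with better survival and quality of life, so this omission alone is unlikely to reverse the conclusion. The issue is a possible bias in the estimate.

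**What to change.** Amend the rule in the Markov model section along these lines: *The scenarios differ in programme costs, in transition probabilities, and in the cost of living-donor work-up that does not lead to LDKT.* Then:

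1. Establish from the cost study whether the transplant and dialysis unit costs include work-ups that ended without donation, and report the answer.
2. Add the excess as an intervention-related cost per educated patient. Use donor evaluations from the 24-month medical-record data where they are recorded, and leave out whatever the unit costs already carry, so that nothing is counted twice.
3. Where no count without the programme exists, run a scenario analysis over a stated range of failed work-ups per extra LDKT. This may well be needed: the implementation study has no control group, and the article does not show that the earlier trial counted evaluations in its control arm.

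The cost is one more uncertain input, a query to the cost study and some extra analysis. Avoiding double counting may need a breakdown of the unit cost that is not readily available; the scenario analysis is the fallback. If an excess exists, the cost-effectiveness figure becomes slightly less favourable.

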#### Model description

A simplified graphical representation of the Markov model showing only the treatment categories, rather than all the individual Markov states is represented in figure 1. Patients continuously enter the model (inflow) at the start of the cycle and can start on haemodialysis, peritoneal dialysis or transplantation. From there they can move between these treatment modalities. Diabetics and non-diabetics are modelled separately since the transition probabilities between the treatment modalities differ between these groups. Since the incidence of kidney failure is increasing, we will also model this in the cost-effectiveness analysis. This will be calculated using data from the database of *Nefrovisie*, a large national database with records of patients with ESRD. As stated before, the model will include probabilistic sensitivity analysis using Monte Carlo simulation. This means that mean numbers of patients per year per treatment modality will be modelled, and the uncertainty surrounding those mean numbers of patients (ie, 95% CIs). Transition probabilities and incidence rates will be based on primary data and will include uncertainty. Costs and utilities will be included in the model as distributions rather than point estimates.

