#### Markov states

The Markov states are based on the treatments currently available in the Netherlands. These are: full care centre haemodialysis, limited care centre haemodialysis, home haemodialysis, continuous ambulatory peritoneal dialysis, continuous cyclic peritoneal dialysis, deceased donor kidney transplantation and LDKT. Since transition probabilities and costs may differ over time, that is, a patient who is in his second year of haemodialysis has a different mortality chance than a patient who just started with haemodialysis, we will define separate Markov states for the first year of treatment and subsequent years of treatment for each specific modality. Incident patients who enter the model and prevalent patients who switch between treatment modalities are assigned to the first year Markov states, whereas patients who spend more than 1 year in any health state are transferred to the subsequent years of that same treatment modality.

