#### Outcomes

The outcome of the implementation will be compared with the baseline situation; the situation before this programme was implemented. The effect size, in terms of an increase in LDKT, will be used from the RCT conducted earlier. Through sensitivity analyses an estimation can be made of the cost-effectiveness of the intervention whether this assumption is either an underestimation or overestimation. A critical assumption will be the extrapolation of the effects after the 2 years.

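### Open, growing inflow inside the cost-effectiveness model makes the cost per QALY depend on the year in which the model stops

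*Protocol article*

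**What the plan says.** The Model description section of the protocol article sets the entry rule: "Patients continuously enter the model (inflow) at the start of the cycle". It then puts growth in that inflow into the economic result itself: "Since the incidence of kidney failure is increasing, we will also model this in the cost-effectiveness analysis". The output it describes is a population count by calendar year: "mean numbers of patients per year per treatment modality will be modelled".

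The Markov model section refers to a horizon ("the time horizon of the study is divided into a number of discrete time periods") but gives no length. It also fixes what differs between the comparators: "besides the costs of the programme, only the transition probabilities will change because of the intervention". Under Markov states, "Incident patients who enter the model and prevalent patients who switch between treatment modalities are assigned to the first year Markov states".

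The reasons given for a dynamic model lie elsewhere. The strengths and limitations box and the Policy implications section name prevalence and the capacity needed for dialysis and transplantation. The Hypotheses section links modelled prevalence to budget allocation and a budget impact analysis. Nowhere does the article say that inflow ends, that entrants are followed until death, or that the cost-effectiveness result is read from a different set of patients than the open population.

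**The concern.** Only programme cost and transition probabilities differ between the comparators. The programme is therefore paid for at entry, while its QALY gains and dialysis savings build up through later time spent with a transplant. An open model always contains patients who have just entered. When it stops, their early costs are in the sum and most of what follows is not. Rising incidence gives these recent entrants more weight.

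A longer horizon shrinks this share, but while inflow continues there are always such patients at the stop. A cohort closed to new entry and run for life settles on a value. The result is meant to support making the programme standard care and will go to the Dutch National Health Care Institute, so the ICER should not turn on a choice of end year.

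**Working it through.** The article gives no ICER, horizon, unit cost, utility or transition probability, so there is no figure of its own to reproduce. The check below shows the mechanism only. **Every input is an assumption.**

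**Inputs.** Yearly cycles; everyone enters on dialysis. Probability of LDKT is 0.05 a year without the programme and 0.20 with it for the first 2 years, then 0.05 in both (a fourfold contrast, like the 17 vs 4 LDKTs in the RCT cited in the Introduction). Death: 0.12 in the first dialysis year, 0.15 in later dialysis years, 0.03 a year with a transplant. Graft failure 0.04 a year, returning to first-year dialysis. Utilities 0.70 (dialysis) and 0.85 (transplant). Programme cost 3,000 at entry. Inflow grows 2% a year. Discounting 4% for costs and 1.5% for effects.

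- Set A: dialysis 80,000 a year, transplant year 90,000, later transplant years 15,000.
- Set B: as A, with dialysis 60,000 and transplant year 120,000.
- Set C: dialysis 70,000, transplant year 100,000, later transplant years 25,000, dialysis death 0.20 throughout.

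**Step 1: what one entrant contributes, by years left in the model** (set A, undiscounted).

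| Years left | Share of lifetime QALY gain | Net incremental cost |
|---|---|---|
| 1 | 0% | +3,000 |
| 2 | 1% | +4,320 |
| 3 | 3% | −1,561 |
| 5 | 9% | −17,932 |
| 10 | 28% | −28,560 |
| 20 | 60% | −15,178 |
| 60 | 100% | +13,491 |

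Check of the second row: 3,000 + (0.20 − 0.05) × 0.88 × (90,000 − 80,000) = 3,000 + 1,320 = 4,320. Net cost rises, becomes a saving, then rises again as patients who live longer go on using care. Truncation can therefore remove savings or remove costs.

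**Step 2: ICER with open inflow stopped at year H.** With ΔC and ΔQ the yearly differences per entrant, e the entry year (0 to H − 1) and t the years since entry:

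ICER(H) = Σₑ 1.02ᵉ Σₜ ΔCₜ/1.04ᵉ⁺ᵗ ÷ Σₑ 1.02ᵉ Σₜ ΔQₜ/1.015ᵉ⁺ᵗ, with t < H − e.

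The followed-out version keeps the same entrants but lets t run to H + 60 − e.

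Check by hand, set B, H = 2:

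- First entrants: 3,000 + 0.15 × 0.88 × 60,000/1.04 = 10,615.
- Second entrants: 1.02 × 3,000/1.04 = 2,942.
- QALYs: 0.15 × 0.88 × 0.15/1.015 = 0.0195, all from the first entrants.
- Ratio: about 695,000.

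**Step 3: results (cost per QALY).**

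| Inflow years | B, stopped | B, followed out | C, stopped | C, followed out |
|---|---|---|---|---|
| 2 | 695,003 | 6,722 | 530,272 | 15,323 |
| 3 | 304,228 | 6,641 | 188,432 | 15,136 |
| 5 | 79,462 | 6,483 | 37,503 | 14,770 |
| 10 | 4,067 | 6,108 | 4,736 | 13,903 |
| 20 | 421 | 5,432 | 8,689 | 12,351 |
| 40 | 3,293 | 4,333 | 10,177 | 9,841 |

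In set A the stopped model gives +369,682 at 2 years and +73,789 at 3, and the programme is dominant (cheaper and more effective) from 5 years. Followed out, it is dominant for every inflow period.

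**Two readings of the table.** First, the followed-out column still drifts. This comes from the assumed unequal discount rates, not from truncation: each year of later entry multiplies a cohort's lifetime ratio by 1.015/1.04, which is 0.784 after 10 years. The inflow period therefore has to be stated even when entrants are followed out. Second, a closed cohort cut short is also unstable (set B: 4,900 at 5 years, dominant at 10, 2,859 at 20), but it settles at 6,568 by 40 years and 6,802 by 60.

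**The case against.** **The article is silent rather than wrong.** It gives no last entry cycle and no horizon length, and a journal article may leave both to the full protocol. This stands in part. A reader might infer that the article says entry continues to the final cycle with no run-out; it does not say so, and a run-out stated elsewhere would remove the problem. What the article does state is continuous entry, with rising incidence carried into the cost-effectiveness analysis. Followed as written, that rule truncates recent entrants at any finite stop.

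**The bias runs against the programme.** A reader might infer this because costs come early and benefits late. The figures do not support it. Short stops overstate the ICER, but at 10 and 20 years the stopped model flatters the programme in sets B and C, because later costs of longer survival and graft failure are also cut off.

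**An open population is a legitimate target.** The Outcomes section compares implementation with the situation before it, and the Hypotheses section looks to all waiting-list patients. That stands, and it would be too strong to say that the model answers the wrong question. The point asks only that whoever enters the ICER be followed out.

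**The article already flags extrapolation.** It does ("A critical assumption will be the extrapolation of the effects after the 2 years"), but that concerns how long the effect persists, not patients cut off at the stop.

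**Following everyone to extinction leans on weak data.** This stands. The Limitations section holds dialysis mortality constant from the second year and says that later data are scarce.

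**Conclusion.** The point holds as a cheap improvement. The article builds continuous, growing inflow into the cost-effectiveness analysis and states neither an end to inflow nor follow-out of entrants. On that rule the ICER depends on the stopping year.

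Neither the direction nor the size is fixed by the article. The illustration rests wholly on assumed costs, utilities, transition rates, growth and discount rates, and shows only that the dependence can be large: in set B, from about 79,500 at 5 years to about 400 at 20, against 6,500 and 5,400 followed out. It does not show that the trial's ICER will be wrong by any given amount. Open inflow remains suitable for prevalence, facility need and budget impact.

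**What to change.** For the ICER, do one of the following and say which:

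- stop inflow after a stated decision period and run the model until all entrants have died; or
- report a lifetime result for one incident cohort plus the prevalent cohort.

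Keep the open model with rising incidence for prevalence, facility need and the budget impact analysis, and state in the Model description which output comes from which version.

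The cost is more cycles and a second read-out of the same spreadsheet. The real downside is that a lifetime run relies more on the constant later-year dialysis mortality acknowledged under Limitations, so that assumption should be varied in sensitivity analysis.
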